### Blood specimen collection

All blood samples (serum and EDTA) are taken before a midweek dialysis session. Before taking blood samples, patients are screened for clinical infection, and those with active infection are examined at a later time point. Blood is sampled in serum and EDTA tubes. Serum tubes are centrifuged. Serum is split into aliquots and frozen at −80 °C. EDTA samples are frozen without further processing allowing later DNA extraction. Routine serum chemistry examinations are performed in ISO certified laboratories in the different centers.

### Screening and eligibility

All patients are reviewed by an ISAR study investigator in the dialysis center for the following inclusion and exclusion criteria:

Inclusion criteriaage ≥18 yearsdialysis vintage ≥90 dayswillingness to participate in at least one technical examination (either ABPM, 24 hour Holter ECG or RVA)written and informed consent.

We plan to recruit a control arm with patients not willing to participate in any technical examination to control for a bias in patient selection, in terms of the possibility that healthier and younger patients are more eager to participate in time consuming examinations.

Exclusion criteriaongoing infectionpregnancymalignant disease having a life expectancy of less than 24 monthslack of written and informed consent.

### Study procedures/measurements

Measurements are performed in incident dialysis patients recruited in one center after the other. The study subjects examinations are performed in the following order: 1) informed consent, 2) measurement of basic clinical data after review of the patient charts, 3) blood samples are taken before the midweek dialysis session, 4) start of 24-h ECG and 24-h ABPM shortly before a midweek dialysis session, 5) retinal vessel analysis before a midweek dialysis session 6) neurocognitive testing before dialysis in a separate room [6]. The study measurements are performed in each center by the same observers. All observers are trained intensively before patient examination.

#### ABPM and pulse wave analysis

The 24-h ABPM and parameters of arterial wall stiffness or their surrogates (e.g., augmentation index (Aix)) are both recorded in the same time period (24 h) using the oscillometric device, Mobil-O-Graph (IEM, Stolberg, Germany) with integrated ARCSolver algorithms (AIT Austrian Institute of Technology, Vienna, Austria) [7, 8]. The Mobil-O-Graph ambulatory BP monitoring device is a very well established and validated device as well for peripheral blood pressure recording [9] and 24-h pulse wave analysis [10–12], also for ESRD patients [13–15]. The classical BP measuring unit in the device has been validated according to the recommendations of the British and European Societies of Hypertension (BHS and ESH) [9, 16]. The method, equipped with a generalized transfer function (GTF) to derive aortic pressure waveforms, is based on brachial readings acquired in the course of the conventional pressure measurement at the diastolic level [7].

Surrogate parameters of central hemodynamics derived by this technique have been validated against the validation gold standard of intra-aortic catheter measurements and have been compared with well-established, non-invasive readings (e.g., tonometry, echocardiography and magnetic resonance imaging [17]) for aortic pressures, wave reflections [8] or aPWV [11]. Clinical usefulness of this method has been demonstrated recently [18]. Furthermore, feasibility [10] and reproducibility [7] of cuff-based Pulse Wave Analysis (PWA) measurements have been reported. The Mobil-O-Graph PWA monitor with integrated ARCSolver algorithms holds approvals from CE, FDA and JPAL.

#### Static and dynamic retinal vessel analysis

##### Measurement with the static retinal vessel analyzer (RVA)

Using a non-mydriatic retinal camera Topcon NW200 (Topcon, Japan), 30° color retinal photographs of each subject were taken and analyzed by means of Visualis and Vessel Map Software (IMEDOS Systems Ltd., Jena, Germany). The diameters of retinal arterioles and venules are measured as described previously [19] and combined into summary indices [20] – the central retinal arteriolar (CRAE) and venular equivalents (CRVE) – which represent the average arteriolar and venular diameters of that eye, respectively. These are additionally expressed as the retinal arteriolar-venular ratio (AVR). The ratio compensates for possible magnification differences between eyes, and an AVR of 1 indicates that arteriolar diameters are, on average, the same as venular diameters in that eye, while a smaller ratio suggests narrower arterioles. AVR < 0.7 has been shown to be associated with microvascular disorder of different kind [21]. This technique has been shown to be highly reproducible [19, 22, 23] and it can be successfully used as a “population screening tool” [21].

##### Measurements with the Dynamic RVA

Twenty minutes after pupil dilation with topical tropicamide drops (Mydriaticum Stulln; Pharma Stulln, Stulln, Germany) continuous simultaneous measurements of retinal vessel diameters of arterial and venous segments are performed in a randomly chosen eye of a subject using a standard protocol of Dynamic Vessel Analyzer (DVA, IMEDOS Systems, Jena, Germany). This protocol consists of 50 s baseline following by 3 cycles consisting of 20 s of flickering light (12.5 Hz, 530 nm), 80 s constant illumination each. Vessel segments of approximately 1 mm in length located in the upper temporal quadrant 1–3 optic disc diameters away from the optic disc edge are assessed.

Properties of DVA and its measurement principles have been previously described in detail [24–26]. The device allows noninvasive online assessment of vessel diameter, depending on times and locations along the vessel. For this purpose, the DVA consists of a retinal camera (450 FF; Carl Zeiss, Jena, Germany), a digital camera for electronic online imaging, and a personal computer for system control, analysis, and recording of the obtained data. Additionally, each measurement is recorded on videotape, which provides a possibility for off-line reassessment of the data. In cases of insufficient data points in the original assessment, additional measurements of retinal arterial reaction can be taken off-line from videotape recordings using DVA.

#### Electrocardiogram (ECG)

The 24-h 12-lead ECG recordings are recorded using the Lifecard CF digital Holter recorder (Delmar Reynolds/Spacelabs, Nuremberg, Germany). ECG and heart rate variability (HRV) analysis are determined by using commercial equipment (Delmar Reynolds/Spacelabs Pathfinder, Nuremberg, Germany) and previously published technologies by use of customized and validated software. An experienced physician blinded to the patient’s clinical status manually reviews and processes all recordings to obtain the sequence of individual R-R intervals together with beat classification (sinus beat, VPC, artifact). Besides, automatic annotation of the ECG is performed for comparison [27]. RR intervals are then further processed. The 24-h ECG recordings are analyzed in terms of traditional parameters, such as QT, QTc, PQ and QRS intervals [28] and left ventricular hypertrophy (LVH) parameters, such as Sokolow-Lyon Index and Cornell Index [29]. For the analysis of the variability of R-R intervals, several HRV parameters are taken. These range from traditional parameters in the time and frequency domain (e.g., standard deviation of the N-N intervals, total power), over further linear (e.g., Poincare indices, the triangular index) to non-linear parameters (e.g., entropy measures, detrended fluctuation analysis) [30–32]. Furthermore, heart rate turbulence (HRT) and deceleration capacity (DC) are calculated according to previously published technologies using established cut-off values. Briefly, HRT quantifies the baroreflex-mediated short-term oscillation of the cycle lengths following ventricular premature complexes [33]. DC quantifies the mean amplitude of all deceleration-related oscillations of heart rate observed in the recording period [34] and is based on a new signal processing algorithm termed phase-rectified signal averaging (PRSA) which is capable of extracting periodic components out of non-stationary, noisy signals [35].

#### Neurocognitive testing

Cognitive function is measured using the Montreal Cognitive Assessment (MoCA) [36]. The MoCA is a short screening instrument for cognitive impairment, which evaluates the domains attention and concentration, memory, orientation, language, visuoconstructional skills, conceptual thinking, calculations and executive functions. Assessment of the latter function is of particular importance, because, apart from memory function, it seems to be impaired early in hemodialysis patients [37, 38]. Cognitive testing is performed under standardized conditions (before dialysis and alone in a separate room), as proposed previously [6].

In addition to MoCA, the Clinical Dementia Rating (CDR) is applied, being the international standard for evaluation of the overall severity of dementia [39]. The assessment includes an interview with an informant or care-giver of the patient, which covers six cognitive and functional domains: memory, orientation, judgment and problem solving, community affairs, home and hobbies and personal care.

### Clinical covariates, endpoints, statistical considerations and data collection

#### Adjudicated baseline comorbidities

Baseline comorbidity is determined by the ISAR Endpoint Committee with two independent reviews and a final review. If a consensus cannot be reached, other members of the committee review the chart and a majority vote of the committee determines the final comorbidity. Comorbidity will be assessed by the original Charlson Comorbidity Index (CCI) [40] and adapted versions of the CCI for ESRD patients [41–43] as far as this data is available from the records at inclusion. Assigned cause of end stage renal disease is obtained from medical record review, kidney biopsy reviews if available and interview with the patient at inclusion.

#### Adjudicated clinical cardiovascular events and outcomes

##### Mortality ascertainment

The observation period for each participant begins at enrollment and continues for 72 months after inclusion. Mortality events are documented from clinic reports, medical records and interviews with the physicians in the dialysis centers.

##### End points

We aim at building a combined dataset to answer questions about the complex and so far only insufficiently understood pathophysiology behind the extreme cardiovascular and non-cardiovascular mortality in dialysis patients. Final goal is the development of a robust model to predict cardiovascular morbidity and mortality and death of all causes in a multivariable Cox-regression analysis. The study end points and serious adverse events are monitored at the time of the follow-up examinations at 24 and 72 months and entered in the study database. Furthermore we will be continuously informed by the dialysis units of the participants death. On notification of a death event we will gather all available clinical information and if in doubt of the correct diagnosis we will contact the next of kin. A panel of three physicians comprising a nephrologist and a cardiologist will independently adjudicate all CV and non CV outcomes based on medical documentation or interview with the local dialysis units. All analyses of end points are based on the following classification by the end-point committee which has to be agreed on by consensus or majority vote.

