##### Adverse events

As the ISAR study is strictly observational, there are no study related adverse events to be expected. All pathological examinations that are found throughout the data acquisition or in the analysis of the data are immediately communicated to the attending physicians.

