#### Ethical considerations

As this study is strictly observational there are no adverse events to be expected that are related to the study. As soon as the study observers find pathological results while evaluating the study examinations, the responsible doctor in the dialysis center will immediately be informed. Furthermore, 24-h Holter ECG and ABPM results of all study participants will be handed to the responsible doctors. There will be no treatment recommendation from the study investigators. The complete responsibility for the treatment of the ESRD patients is in the hands of the responsible doctors in the dialysis centers.

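### Causes of death and CV events are classified from dialysis units that already hold each patient's Holter and ABPM results, so cause-specific associations with these markers can be biased

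*Protocol article*

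**What the plan says.** The protocol article sets out two procedures in different sections.

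**Where the outcome classification comes from.** Under Mortality ascertainment: "Mortality events are documented from clinic reports, medical records and interviews with the physicians in the dialysis centers". Under End points, once a death is reported, "we will gather all available clinical information and if in doubt of the correct diagnosis we will contact the next of kin". Classification then falls to three physicians, who "will independently adjudicate all CV and non CV outcomes based on medical documentation or interview with the local dialysis units", and the result is settled by consensus or majority vote. Because of the word *or*, an interview with the unit can be the only source.

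**Who holds the marker results.** Under Ethical considerations: "24-h Holter ECG and ABPM results of all study participants will be handed to the responsible doctors". Under Adverse events, pathological examinations "that are found throughout the data acquisition or in the analysis of the data are immediately communicated to the attending physicians".

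The ABPM and ECG objectives ask whether 24-h ABPM and baseline autonomic dysfunction predict cardiovascular mortality, death from infection and hospitalization by cause, alongside all-cause mortality. Statistical analysis plans cause-specific hazards for the competing causes of death. In these assessments the only blinding described is that of the Holter reader to the patient's clinical status. That protects the marker measurement, not the outcome classification.

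**The concern.** Taken together, these procedures make the people who know a patient's Holter and ABPM results a source for deciding whether that patient's event was cardiovascular. If such knowledge sways the account of a doubtful death, more deaths will be called cardiovascular in patients with an abnormal marker and fewer in patients with a normal one. An association with cardiovascular death can then appear or grow, with an opposite shift for non-cardiovascular death, including death from infection.

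The most plausible place is unwitnessed sudden death. Under Outcomes, such a death is suspected to be sudden cardiac death if the patient was seen in a stable state during the preceding 24 hours. That is a judgement, and the facts for it may come from the unit. The Discussion puts sudden cardiac death at half of cardiovascular deaths, so the category is not small.

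At stake are the cause-specific research questions and the cardiovascular part of the planned prediction model.

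**Working it through.** **1. The plan's own figures.** Sample size: 500 × 20% = 100 deaths in 2 years. For the balanced comparison, 250 × 0.25 + 250 × 0.15 = 62.5 + 37.5 = 100. Power for 25% vs 15% with 250 per group, two-sided 5%, pooled normal approximation, is 80.0%, as stated. It concerns all-cause mortality and is untouched by this point.

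**2. The bias path.**
- Holter and ABPM results go to the responsible doctors for all participants (Ethical considerations).
- Those doctors are interviewed, and their records are among the sources (Mortality ascertainment, End points).
- The same markers are tested against outcomes split by cause (ABPM and ECG objectives, Statistical analysis).

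No step depends on a detail left out of the article. Whether the panel itself sees the results is not stated. The informants do have them.

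**3. Possible size.** Inputs from the document: 100 deaths (Sample size), 50% cardiovascular (Discussion, Electrocardiogram), two-sided 5% (Statistical analysis). Assumptions: two equal marker groups; a marker unrelated to death, hence 50 deaths per group; a share *a* of deaths with ambiguous cause; an ambiguous death called cardiovascular with probability *q* if the marker is abnormal and 1 − *q* if normal. Clear deaths split evenly. Expected cardiovascular deaths:

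- abnormal: x = 50 × [(1 − a)/2 + a·q]
- normal: y = 50 × [(1 − a)/2 + a·(1 − q)]

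SE of the log ratio = √(1/x + 1/y); z = ln(x/y)/SE; false-positive rate = Φ(−1.96 + z) + Φ(−1.96 − z).

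| a | q / 1 − q | x vs y | Ratio x/y | False-positive rate |
|---|---|---|---|---|
| 10% | 0.6 / 0.4 | 25.5 vs 24.5 | 1.04 | 5.2% |
| 10% | 0.7 / 0.3 | 26 vs 24 | 1.08 | 5.9% |
| 20% | 0.7 / 0.3 | 27 vs 23 | 1.17 | 8.7% |
| 30% | 0.8 / 0.2 | 29.5 vs 20.5 | 1.44 | 24.4% |

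Example, last row: x = 50 × (0.35 + 0.24) = 29.5; y = 50 × (0.35 + 0.06) = 20.5; SE = √(1/29.5 + 1/20.5) = 0.288; z = 0.364/0.288 = 1.27.

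Non-cardiovascular deaths mirror this: 20.5 vs 29.5, ratio 0.69, in the last row. Total deaths stay at 50 vs 50 in every row, which is why all-cause mortality is unaffected.

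**4. A second model.** Suppose a share *m* of non-cardiovascular deaths is called cardiovascular in the abnormal group only. Then the ratio is 1 + m. Simulation gives a false-positive rate of 5.3% at m = 5%, 10.1% at 20% and 25.2% at 40%. With 200 deaths, an assumed figure for longer follow-up, m = 20% gives 15.8%: the ratio stays the same while the error rate grows.

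**The case against.** The strongest reply is that the document never sends Holter or ABPM reports to the panel. They go to the treating doctors, and the panel's sources are wider than the unit's file: clinic reports, all available clinical information, and next of kin in doubtful cases. Dossier content and panel masking usually belong in an endpoint charter, which is not shown. This stands. A reader might infer that the plan delivers the predictor to the outcome assessors; the text supports only that the informants know it and that the files may contain it. But masking the panel would not by itself remove the influence of unmasked informants, and independent review with a majority vote does not correct a source that all three share.

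Other stronger readings also fail:

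- *The sudden-death definition depends on the Holter.* Its criteria do not use a Holter result, and much of the remaining cardiovascular list rests on harder facts such as troponin change, ECG and revascularization.
- *The autonomic indices themselves are disclosed.* The article does not say that heart rate variability, turbulence or deceleration capacity are in the Holter results handed over.
- *Comparisons with PWV or retinal markers are distorted.* This cannot be derived. PWV comes from the same device and the same 24 h as ABPM, and pathological findings from all examinations are communicated.
- *Comorbidity scoring by the Endpoint Committee is an error.* Cardiac history is in any chart used to classify a death, and one committee holding both roles is common.

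Finally, the study calls itself explorative, and at the low end of the assumptions the bias is negligible.

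**Conclusion.** The concern holds in limited form. The document states both that the treating doctors receive every participant's Holter and ABPM results and that those doctors and medical documentation inform the classification of outcomes. Cause-specific associations with these markers can therefore be biased, most plausibly through unwitnessed sudden death. The influence is possible, not certain, in any one case.

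The documents give no misclassification rate, so the size is unknown. Over the assumed range, a null marker would show a cardiovascular-death ratio of about 1.04 to 1.44 and be declared significant in about 5% to 24% of analyses instead of 5%. These figures rest on the assumed ambiguity and tilt, equal marker groups and the 2-year count of about 100 deaths. All-cause mortality, the 2-year survival model and the power calculation are unaffected.

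**What to change.** Add to End points, for events still to be adjudicated:

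- The panel works from event dossiers from which the study office has removed the ISAR baseline examination results.
- Interviews with the units follow a fixed event questionnaire that does not ask for study examination results.
- Classifications resting on an interview alone are flagged.
- Sensitivity analyses of the cause-specific endpoints exclude interview-only classifications and handle unwitnessed sudden cardiac death separately.

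Reporting of results to the treating doctors stays exactly as it is. The cost is some clerical redaction and probably a few more deaths of undetermined cause. The Conclusion says that follow-up examinations are under way, so later events can still be covered, although the article does not show what share of events that is.

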##### Outcomes

Major cardiovascular events are defined as:Sudden cardiac death (SCD) defined as a sudden pulseless condition out of the hospital (most probably due to arrhythmia). If the event is unwitnessed SCD will be suspected if the patient has been seen stable within the last 24 h preceding the event.fatal or non-fatal myocardial infarction (MI), defined as chest pain, dynamic troponin change, cardiogenic shock and original ECG or ECG report to distinguish ST-elevated MI vs. non-ST-elevated MI.need for coronary revascularization (coronary artery bypass graft/percutaneous coronary intervention(PCI)/percutaneous transluminal coronary angioplasty) or death after cardiovascular procedure/operation (e.g. cardiac valve surgery, PCI)Death or hospitalization due to congestive heart failure (CHF).ischemic stroke (defined as an acute focal neurologic deficit of sudden onset attributed to the occlusion of a cerebral arterial vessel by a thrombus), non ischemic-stroke (due to major bleeding)

Major non-cardiovascular, non-cerebrovascular events are defined as:Death or hospitalization due to infection or sepsis (pneumonia, urogenital infection, gastrointestinal, endocarditis, shunt infection, cutaneous infection, meningitis)Death or hospitalization due to malignancyDeath due to chronic lung disease (chronic obstructive pulmonary disesase (COPD), asthma, emphysema, pulmonary hypertension)Gastrointestinal death (bleeding, pancreatitis, malnutrition)Death or hospitalization due to trauma or accidentDeath or hospitalization due to other causes

##### Adverse events

As the ISAR study is strictly observational, there are no study related adverse events to be expected. All pathological examinations that are found throughout the data acquisition or in the analysis of the data are immediately communicated to the attending physicians.

#### Sample size

It is intended to recruit a number of patients that allows to detect relevant differences in mortality between groups of interest and that provides sufficient information for development of a multivariable predictive model for mortality. With an included number of 500 patients, we expect to observe about 100 deaths within the follow-up period of 2 years, based on an assumed 2-year mortality rate of 20 % in our population of dialysis patients [44]. So the study is sufficiently powered (power of about 80 %) to detect differences in mortality between two balanced groups (*n* = 250 patients per group, if the true difference in 2-year mortality between the groups is 10 percentage points (25 % vs. 15 %). For a comparison of two unbalanced groups with sizes of 100 and 400 individuals, e.g. for comparison of groups with presence and absence of a potential risk factor, a true difference in 2-year mortality of 30 % vs. 17.5 % could be detected with a probability (=power) of about 80 %. These differences seem realistic considering reported figures from recent studies [44, 45].

In order to model the hazard rate using a multivariable Cox regression model, the number of observed events is the “limiting sample size” [46]. Based on various simulation studies, the number of predictors that can be included in a multivariable regression model that is likely to provide reliable results is assumed to lie within “limiting sample size divided by 5″ and “limiting sample size divided by 20” [46–48]. Consequently, with a sample size of 500 patients leading to an expected number of 100 observed events, about 10 to 15 predictor variables can be included in a multivariable Cox regression model, which appears to be an adequate number given possible candidates and previously proposed prediction models for mortality in dialysis patients [44].

